## **Funder**

This research study is being undertaken as part of a Pre-Doctoral Research Fellowship that has been awarded to the Principal Investigator (PI), [name], by the Imperial Health Charity (IHC) and is being funded by the National Institute for Health and Care Research (NIHR) Imperial Biomedical Research Centre (BRC).

The study has been peer-reviewed by the IHC fellowship committee before the decision to fund and the proposal has also been supported by the Intensive Care Lead Nurse at Hammersmith Hospital and members of the public with lived ICU experience.

## GLOSSARY OF ABBREVIATIONS

|         |                                                 |
|---------|-------------------------------------------------|
| BRC     | Biomedical Research Centre                      |
| CAM-ICU | Confusion Assessment Method                     |
| CI      | Chief Investigator                              |
| GCP     | Good Clinical Practice                          |
| GDPR    | General Data Protection Regulation              |
| GP      | General Practitioners                           |
| IHC     | Imperial Health Charity                         |
| NHS     | National Healthcare Service                     |
| HRA     | Health Research Authority                       |
| ICHT    | Imperial College Healthcare NHS Trust           |
| ICF     | Informed Consent Form                           |
| ICU     | Intensive Care Unit                             |
| ISF     | Investigator Site File                          |
| QoL     | Quality of Life                                 |
| NIHR    | National Institute for Health and Care Research |
| PI      | Principal Investigator                          |
| PIS     | Patient Information Sheet                       |
| PPI     | Patient and Public Involvement                  |
| RASS    | Richmond Agitation-Sedation Scale               |
| REC     | Research Ethics Committee                       |
| SI      | Sub-Investigators                               |
| SoA     | Schedule of Assessments                         |

## KEYWORDS

Critical care; Delirium; Family involvement; Non-pharmacological interventions; Nurses

## STUDY SUMMARY

|                         |                                                                                                                                                                                                                                                                                                                                                                                                                                                                                                                                  |
|-------------------------|----------------------------------------------------------------------------------------------------------------------------------------------------------------------------------------------------------------------------------------------------------------------------------------------------------------------------------------------------------------------------------------------------------------------------------------------------------------------------------------------------------------------------------|
| TITLE            | DaCsi-ICU: The use of auditory-visual stimulation to reduce delirium rates in intensive care patients' post-cardiac surgery: a feasibility study                                                                                                                                                                                                                                                                                                                                                                                 |
| DESIGN           | This study is a mixed methods research design that includes collection of data through interviews, quality of life questionnaires and patients' medical records.                                                                                                                                                                                                                                                                                                                                                                 |
| AIMS             | 
 
▪ Determine the incidence of ICU delirium in ICHT following cardiac surgery
 
▪ Explore the compliance of outcome measures that diagnose ICU delirium
 
▪ Implement a family-focused sensory stimulation programme in the ICU
 
▪ Evaluate its useability and potential impact in patients, families and ICU staff
 
                                                                                                                                        |
| OUTCOME MEASURES | 
This study endpoints are to:
 
 
1. Assess the useability/practicalities of implementing a family-focused sensory stimulation to improve ICU delirium outcomes in patients undergoing cardiac surgery
 
2. Develop an innovative nurse-led tool to improve delirium outcomes in ICU post-cardiac surgery
 
3. Explore the acceptability of a new programme to be implemented in cardiac ICU, amongst critical care staff, patients and family members/friends
 
 |
| POPULATION       | 30 study participants                                                                                                                                                                                                                                                                                                                                                                                                                                                                                                            |
| ELIGIBILITY      | Study eligibility criteria is specific for each care group.                                                                                                                                                                                                                                                                                                                                                                                                                                                                      |
| DURATION         | 24 months at Hammersmith Hospital, ICHT                                                                                                                                                                                                                                                                                                                                                                                                                                                                                          |

## **1. INTRODUCTION**

Delirium can affect over 50% of patients following cardiac surgery in intensive care units (ICU), leading to long-term cognitive impairment, prolonged hospital stays and increased costs to the NHS. Nurse-led auditory-visual stimulation to help prevent and manage ICU delirium is a relatively novel and unexplored clinical practice in the postoperative cardiac field.

This study aims to assess the feasibility of an innovative intervention using family focused sensory stimulation to reduce delirium in ICU patients following major cardiac surgery and improve post-surgical outcomes.

### **1.1. BACKGROUND**

Delirium is a common and often undiagnosed brain dysfunction that occurs in ICU and is associated with increased morbidity and mortality [1,2]. Its incidence can vary between 30-80% depending on various risk factors, doubling the National Health Service (NHS) inpatient cost per patient compared to those without delirium [3,4]. It is a complex, distressing and debilitating condition that impacts patients, family members and healthcare professional [5].

Patients undergoing cardiac surgery are a particularly vulnerable group as ICU delirium affects up to 55% of these patients, due to operative reasons including surgical complexity and cardiac bypass time [6,7]. Delirium is associated with increased anxiety and depression, poor functional status, increased risk of stroke and significant cognitive impairment up to a year post-cardiac surgery. It has also been linked with an elevated number of hospital readmissions, longer ICU and hospital lengths of stay [8,9].

Given the significant burden on patients and the NHS, delirium prevention and management is considered to be national priority in ICU by the James Lind Alliance [10]. Delirium is potentially preventable and healthcare professionals must diagnose this condition in critical care units by using the Confusion Assessment Method (CAM-ICU) screening tool as per the UK National Institute for Health and Care Excellence (NICE) guidelines [11,12]. Whilst pharmacological interventions are the mainstay of treatment in ICU, the Society of Critical Care Medicine highlights the importance of non-pharmacological therapies in the management of ICU delirium [2]. Therefore, there is an urgent unmet need to identify novel non-pharmacological management strategies to prevent and treat ICU delirium [10].

### **1.2. RATIONALE FOR CURRENT STUDY**

In recent years, family involvement has become a major theme in the literature when debating about patient outcomes in the healthcare system. Several studies developed in intensive care units have demonstrated positive results when involving family members in patient's care plan. More analysis has shown the possible combination between family involvement and sensory stimulation when reducing anxiety and depression in ICU patients [8].

An intriguing potential therapy is the use of auditory and visual sensory stimulation combined with family involvement/interventions, which could potentially improve delirium outcomes. A meta-analysis demonstrated that non-pharmacologic therapies involving family members leads to a 24% risk reduction of ICU delirium [13]. A similar analysis shown that family involvement

in patient care was the most effective intervention in reducing ICU delirium incidence, compared to sedation reduction and exercise programmes [14]. Another study also concluded the reduction of delirium in ICU patients when exploring the impact of an auditory reorientation intervention involving family members [15]. Additionally, a feasibility study reported the acceptance by elderly patients and hospital staff of a family auditory and visual sensory intervention that was implemented in ward-based patients with dementia [16].

There is a paucity of information on this type of interventions, especially in ICU patients post cardiac surgery. Therefore, further studies are urgently required to investigate the use of family-centred sensory stimulation in ICU delirium prevention and management following major cardiac surgery.

## **2. STUDY OBJECTIVES**

Research question: Is a family focussed auditory-visual stimulation feasible and acceptable to be delivered in a critical care setting to patient's post-cardiac surgery to reduce ICU delirium?

### **2.1. STUDY PRIMARY OBJECTIVES**

Based on the research question, the primary aim of this research study is to:

- Evaluate the feasibility and acceptability of introducing an auditory and visual sensory stimulation intervention involving family members as part of prevention and management strategies for ICU delirium in patients following cardiac surgery.

### **2.2. STUDY SECONDARY OBJECTIVES**

The secondary objectives to this study are to:

- Determine the incidence of newly diagnosed ICU delirium patients following cardiac surgery in the Imperial College Healthcare NHS Trust (ICHT);
- Investigate the compliance of primary outcome measures that diagnose patients with ICU delirium;
- Implement a sensory stimulation programme with family-focused auditory-visual cues in ICU;
- Assess the practicalities of implementing a sensory stimulation programme and the potential impact on patients, family members and critical care staff.

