## **3. STUDY DESIGN**

The study will be conducted over twelve months in the Cardiac Intensive Care Unit at Hammersmith Hospital, Imperial College Healthcare NHS Trust. For this study, a total of 30 individuals (12 patients, 12 family members or close friends and 6 critical care nurses) will be recruited and interviewed to allow sufficient depth and richness of data. Patients and family members/friends will be mainly recruited from the ICHT pre-operative clinic outpatient department, which runs several pre-operative clinics per week. Each week, approximately eight patients undergo cardiac surgery, and the research team intends to recruit one patient and their family member/friend per a week for a period of 4 months.

All participants will be given time to consider their participation in the study and if happy will be consented by PI or other delegated member of the research team. Patients will be approached during one of their pre-operative clinic appointments and informed consent will be sought at this stage. Once written consent has been obtained, patients will be asked to nominate a family member or friend to be contacted by the PI. After signing the consent form, family members/friends will also be enrolled into the study and requested to self-record short videos pre-operatively (based on a guided script - ANNEX XIII), which will be safely uploaded to an iPad. In addition, patients will be requested to select multiple pictures, which will be securely uploaded into a digital photo frame. This package combination of videos and pictures will be shown to patients post-operatively in ICU. Critical care nurses will be recruited after they have provided direct care to at least one participant, who received the study intervention in ICU.

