##### **4.3. EXCLUSION CRITERIA**

###### **PARTICIPANTS**

- Female and male patients under the age of 18
- Unable to consent to the study pre-operatively
- Significant hearing/visual impairment
- Participants with learning disabilities, pre-existing delirium, dementia or other significant underlying cognitive morbidity
- Moribund participants, likely to die in the next 24 hours
- Participants that do not speak English language

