## **6. STUDY ASSESSMENTS**

### **6.1. ASSESSMENT AND FOLLOW UP**

#### **STUDY INTERVENTION**

The intervention will require family members/friends (selected by patients) to self-record short videos (during the preoperative stage) based on a carefully drafted guided script divided into two parts: a) Reorientation (discussing date/time/surroundings, family members on the video); b) Reassurance (providing comforting/supportive messages). Videos will be recorded either with a video-recorder device (provided by the research team) in the pre-operative clinic or at home using a personal smartphone. At a later stage, videos will be sent to an encrypted NHS email and securely uploaded in line with ICHT Information Governance to a password-protected iPad, which will also facilitate family-patient video calls in ICU. In addition, patients will be requested to select personal pictures pre-operatively, which will be also sent to the PI's encrypted NHS email and securely uploaded into a special digital photo frame with reference to time and date.

Digital photos will be shown continuously at the patient's bedside for 12 hours a day (between 8am to 8pm) and different family videos will be played three times at specific hours of the day (9am, 2pm and 7pm) throughout their stay in ICU. Additionally, videos will be also played upon patient request and last video shown that day will be re-played. In occasions when patients develop ICU delirium and considering personal consultee's agreement, the last video shown to participants will be re-played and patients will be closely monitored. This will help the research team to understand if the combination of personal pictures and family videos impacted patients' orientation and reassurance and if, ultimately, promoted the reduction of ICU delirium. The PI will be responsible for setting up the required equipment and delivering the intervention alongside ICU nurses as illustrated in the study diagram below (Annex XI).

The draft guided script of reorientation and reassurance messages was initially developed based on published research and considering patients' memories from their lived ICU experience(s) [15]. Subsequently, it was further refined within a lay focus group of patient and public members (with ICU lived experience) and reviewed by an expert panel comprising two critical

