## **7. STATISTICS AND DATA ANALYSIS**

The study sample size was based on sample size based on previous feasibility studies and complexity of the planned intervention [18]. Considering the study design and timelines, the recruitment target for this study is 12 patients alongside 12 family members. The research team also plans to recruit 6 critical care nurses to be able to collect more in-depth data about the study intervention acceptance in ICU.

**Quantitative data** will be analysed using SPSS statistical software. Descriptive statistics will be used to present demographic data, medical characteristics and causal beliefs about ICU delirium. Correlations will be used to examine the relationships between vital signs, new ICU prescriptions, ICU complications, mortality rates and delirium status. Logistic regression analyses will be applied when investigating the influence of sociodemographic and clinical factors on the identification of patients with ICU delirium.

**Qualitative data** from interviews will be audio-recorded, transcribed verbatim and managed in NVIVO. Framework analysis will be used to systematically manage and holistically interpret qualitative data collected from the interviews. The academic supervisors, [name], [name] and the CI, [name], will be involved in reviewing transcripts, developing the coding frame and identifying potential themes for subsequent exploration. Additionally, the PI will compare concepts from existing literature with those emerging from this study. After identifying the initial themes, the lead researcher will also liaise with a patient and public involvement (PPI) advisory group to check the credibility and usefulness of the selected themes and findings.

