| 5 | Did the patient look at the digital photo frame during the day?                                     |  Yes  No
If “Yes”, how many times: ____                                                                                                                                                                                     |
| 6 | Did the intervention impact ICU nursing care?                                                       |  Yes  No
If “Yes”, please specify: ____                                                                                                                                                                                     |
| 7 | Was the family intervention delivered without any untoward events (eg., acute distress)?            |  Yes  No
If “No”, please specify: ____                                                                                                                                                                                      |
| 8 | Did the patient request to watch the video more than 3 times a day?                                 |  Yes  No
If “Yes”, please specify the total number of times: ____                                                                                                                                                           |
| 9 | Did the patient develop delirium during the day (8am-8pm)?                                          |  Yes  No
9a. If “Yes”, was the video played again?
 Yes  No
9b. If “Yes”, did it improve delirium status?
 Yes  No |

Table 2. Nursing Checklist Night-time

| N | Nursing Checklist Night-time (8pm – 8am)                          | Tick as appropriate                                                                                                                                                                                                                                                            |

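### The delirium incidence objective names the whole Trust, but the data describe only 12 selected, treated patients, and with no comparator they cannot show a reduction

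*Protocol*

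**What the plan says.** **Incidence.** The first secondary objective in Protocol Section 2.2 is: "Determine the incidence of newly diagnosed ICU delirium patients following cardiac surgery in the Imperial College Healthcare NHS Trust (ICHT". The Aims row of the Study Summary puts the same aim first.

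**Who is studied.** Section 3 states that "a total of 30 individuals (12 patients, 12 family members or close friends and 6 critical care nurses) will be recruited and interviewed", and Section 7 confirms that "the recruitment target for this study is 12 patients alongside 12 family members". Patients come mainly from the pre-operative clinic. They must speak English, have capacity to consent before surgery (Sections 4.2 and 4.3), and nominate someone willing to record videos. Among the exclusions is: "Participants with learning disabilities, pre-existing delirium, dementia or other significant underlying cognitive morbidity". Under Sections 3 and 6.1 every enrolled patient is to receive the photo and video package.

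**Effect.** Section 6.1 says the data will help the team understand whether the pictures and videos affected orientation and reassurance "and if, ultimately, promoted the reduction of ICU delirium". In Annex XII, items 9b (day) and 4b (night) ask the nurse, after a replay prompted by delirium, "did it improve delirium status", with a yes/no box.

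**Timing.** Annex I schedules CAM-ICU and RASS from D0 and the family intervention from D1.

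**The concern.** An incidence for a Trust's cardiac surgery patients needs either all of those patients or a representative sample, observed under usual care. The plan has a small, selected group observed under an intervention aimed at the very outcome being counted. If the report follows the objective's wording, it will present a treated-group proportion as the Trust's rate, and a reader could take it for an untreated background rate.

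The Section 6.1 sentence raises a related problem. It assigns the delirium data a causal use, but the protocol describes no control group, historical rate or before-after comparison. The two checklist items invite the nurse to make the same causal judgement one episode at a time.

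**Working it through.** **1. The plan's own figure.** 12 + 12 + 6 = 30, which agrees with Section 3. The 12 itself cannot be reproduced: Section 7 says it is "based on previous feasibility studies and complexity of the planned intervention" and gives no precision, rate, alpha or power.

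**2. Objective and data side by side.**

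| | Objective (Section 2.2, Study Summary) | Data (Sections 3, 4.2, 4.3, 6.1) |
|---|---|---|
| Patients | Cardiac surgery patients in the Trust | 12 consenting English speakers, mainly from the pre-operative clinic |
| Cognitive risk | No restriction | Pre-existing cognitive problems excluded |
| Family | No restriction | A willing relative or friend is needed |
| Care | Not specified, so naturally read as usual care | Package meant to prevent delirium, for all |

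The pre-screening data in Section 4.5 on other patients are limited to name, age, hospital number and dates. No unit-wide delirium count is therefore planned that could fill the gap.

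**3. Precision at n = 12.** The exact (Clopper-Pearson) 95% limits for x cases in n are the 2.5% point of Beta(x, n − x + 1) and the 97.5% point of Beta(x + 1, n − x).

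| Cases | Observed | Exact 95% CI |
|---|---|---|
| 4/12 | 33% | 9.9% to 65.1% |
| 6/12 | 50% | 21.1% to 78.9% |
| 7/12 | 58% | 27.7% to 84.8% |

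Section 1.1 cites an ICU delirium range of 30% to 80%, a span of 50 points. The 6/12 interval covers 78.9 − 30 = 48.9 of those points, and the 7/12 interval covers all of them. Either result would hardly narrow what the protocol already cites.

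**4. Would more patients of the same kind help?** A half-width of 10 points at a rate of 50% needs 1.96² × 0.25 / 0.10² = 96.04, so 97 patients. That would cure the imprecision only. The selection and the universal treatment would remain.

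**5. What the unit could supply.** Section 3 says: "Each week, approximately eight patients undergo cardiac surgery". Four months is 52/12 × 4 = 17.33 weeks, so about 17.33 × 8 = 139 operations, of which 12 is about 9%. CAM-ICU is already assessed twice daily as routine (Section 3). A count over all 139 would give a half-width of 1.96 × √(0.25/139) = 0.083, or about 8 points. With 16 weeks (128 operations) it is 0.087. Both figures assume complete recording.

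**6. Effect.** With one treated group there is no untreated rate to subtract, whatever proportion is observed. The same holds for a single replay: a patient who is CAM-ICU positive at one check may be negative at the next without any video. The protocol gives no figure for how often that happens, so I attach no size to it.

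**7. Timing.** With CAM-ICU from D0 and the intervention from D1 in Annex I, some delirium may begin before any exposure. Section 4.6 has the study resume in ICU after the patient re-consents, so first exposure may come later still.

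**The case against.** The strongest reply is that this is a feasibility study and says so. Section 2.1 limits the primary aim to feasibility and acceptability, Section 2.2 speaks only of potential impact, and Section 7 plans descriptive statistics, correlations and logistic regression, with no test of the intervention. That stands. It is why the point concerns wording and recording, and not the design or the 12 patients.

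A reader might infer more than the protocol supports:

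- *That reducing delirium is a stated study objective.* It is not in Sections 2.1, 2.2 or 3.1. Section 6.1 says only that the data will help the team understand the question. Where Section 3 mentions reducing incidence, it gives the purpose of playing the videos, not an analysis.
- *That the nurse's tick-box is the only measure of response.* CAM-ICU is assessed twice daily and collected, Annex I schedules CAM-ICU and RASS on D0 to D3, and CAM continues on the ward. What is missing is a field for the time of a replay prompted by delirium, which would link it to those assessments.
- *That delirium before and after first exposure will be pooled.* No section says so, and daily assessments allow a split. D0 is not clearly unexposed either, since Section 3 could be read as showing photos soon after surgery.
- *That the study is underpowered for an effect.* No such test is planned. A hypothetical one-sided exact 5% test against a fixed rate would have 19% power at 55% (reject at 3 or fewer of 12) if the 24% reduction in Section 1.2 is relative. Over base rates of 30% to 80% the power runs from 4% to 31%, and at 55% it is about 46% if the 24% is absolute. The conclusion rests on the missing comparator, not on these figures.
- *That the enrolled patients are low-risk.* The exclusions point that way, but no figure shows it.

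None of this rescues the incidence objective. It is stated twice for the Trust, and no analysis plan could supply patients who are not observed.

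**Conclusion.** The incidence objective is wrong as written and should be fixed. The study can report the proportion of enrolled intervention recipients who develop delirium, with an interval nearly 58 points wide at 6/12 (78.9 − 21.1 = 57.8). It cannot report the Trust's incidence. The Section 6.1 sentence gives the data a use that a single group without a comparator cannot serve. It is a lesser fault, because reduction of delirium is neither a listed objective nor a planned test.

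The mismatch of population and treatment follows from the protocol's text and needs no assumption. The intervals assume that all 12 patients contribute delirium data; losses would widen them. The checklist and D0/D1 points are matters of making the descriptive data readable, not errors of analysis.

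**What to change.** 1. **Study Summary (Aims) and Section 2.2.** Restate the objective as the proportion of enrolled intervention recipients with at least one positive CAM-ICU, with an exact 95% CI and no claim for the Trust as a whole. If the unit's rate is wanted, take it from anonymised aggregate counts of routine CAM-ICU in all cardiac surgery patients over the same months. Report how complete the recording is, since compliance with that measure is itself a secondary objective.
2. **Section 6.1.** Reword the sentence so that delirium data are descriptive, and state that no effect on delirium will be inferred.
3. **Annex XII, items 9b and 4b.** Replace the yes/no opinion with the time of the replay, to be read beside the routine CAM-ICU and RASS before and after it.
4. **Onset.** Describe delirium that begins before first exposure separately. The daytime checklist (item 3) already asks for the times of the planned video deliveries.

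The cost is a few reworded sentences, two changed checklist lines and more modest stated aims. The optional unit count needs a separate request for aggregate data. Recruitment, the sample of 12 and the primary feasibility aim are unchanged.
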